**Table 6 LIST OF ABBREVIATIONS**

| **Abbreviation** | **Full term** |
| --- | --- |
| ADM | Antidepressant Medication |
| AE | Adverse Event |
| AES | Advanced Encryption Standard |
| AI | Artificial Intelligence |
| AR | Adverse Reaction |
| CI | Chief Investigator |
| CBT | Cognitive Behavioural Therapy |
| CRF | Case Report Form |
| CRO | Contract Research Organisation |
| DMC | Data Monitoring Committee |
| DMEC | Data Management and Ethics Committee |
| eCRF | Electronic Case Report Form |
| EDC | Electronic Data Capture Form |
| EXSW | Female veterans |
| GAD | Generalised Anxiety Disorder |
| GCP | Good Clinical Practice |
| GDPR | General Data Protection Regulation |
| IM | Iona Mind |
| Iona SHAM CONTROL | Iona Mind SHAM control app |
| IonaFFV | Iona Mind app for Female Forces Veterans |
| ISRCTN | International Standard Randomised Controlled Trials Number |
| ITT | Intention to Treat |
| LICBT | Low-Intensity Cognitive Behaviour Therapy |
| mCBT | Mobile Cognitive Behavioural Therapy |
| MAUQ | Mobile Acceptability and Usability Questionnaire |
| PHQ-9 | Patient Health Questionnaire-9 |
| PI | Principal Investigator |
| pRCT | Feasibility Randomised Controlled Trial |
| PROM | Participant Reported Outcome Measures |
| REC | Research Ethics Committee |
| SAE | Serious Adverse Event |
| SAP | Statistical Analysis Plan |
| SAR | Serious Adverse Reaction |
| SOP | Standard Operating Procedure |
| TIDieR | Template for Intervention Description and Replication Checklist |
| UNEXE | University of Exeter |
| WASAS | Work and Social Adjustment Scale |

Figure 1: Illustration of Feasibility RCT comparing Iona Mind (IonaFFV) AI driven mobile phone app for the treatment of depression in female veterans with a SHAM control app (Iona SHAM CONTROL)

[figure not shown]

[figure not shown]

### 1 BACKGROUND

Help-seeking barriers to mental health services experienced by female veterans result in them being underserved and underrepresented compared to female serving, civilian or male Armed Forces Veterans (Leung et al., 2020). Current NHS England data demonstrates 1,500 female veterans only accessing NHS Talking Therapies for Anxiety and Depression or Op COURAGE statutory mental health services per annum. If these numbers are compared with access rates of serving women, the general population, or male veterans they are approximately 50% of what would be expected. Low uptake of mental health services by female veterans in the UK suggests services and interventions are not well adapted to their needs and requires adaptation to enhance engagement.

Research highlights adaptations to areas such as language, imagery and tailoring specific Cognitive Behavioural Therapy (CBT) written self-help interventions to target armed forces veterans enhances acceptability (Farrand et al., 2019). In this study however, participants were exclusively male and the extent that preferences are consistent with those held by female veterans is largely unknown. Furthermore, little is known regarding the extent that preferences may equally be applied to intervention formats such as digital mobile phone apps and if provided through community organisations representing the interests of female veterans. Increased knowledge is therefore important given the small number and wide geographical distribution of female veterans that makes it difficult to offer bespoke and cost-effective sustainable services. Challenges are amplified when current commissioning arrangements remain focussed on statutory mental health services rather than considering wider community-based options. Limited options are significantly problematic given serving females experience high levels of mental health difficulties (Jones et al., 2020), making increased prevalence of mental health difficulties experienced by female veterans likely.

Developing acceptable, scalable and cost-effective interventions delivered by mobile digital apps represents a solution, with good levels of acceptability for female veterans (MeTVeT study; Parkes et al., 2022) justify this proposal to co-develop an app targeting female veterans. Utilising apps to treat mental health difficulties is novel, innovative and can limit stigma, concerns regarding confidentiality or future employment prospects and consistent with female veterans’ self-management preferences (Farrand et al., 2019). When examining the development of apps to support delivery of mental health interventions however, consideration is still required to the evidence-base. Currently, the National Institute for Health and Care Excellence (NICE) restricts recommendations to CBT self-help interventions only when supported by a psychological practitioner for depression (NG222; 2022) and generalised anxiety (CG113; 2020). However, the NHS has begun to successfully implement digital interventions for common conditions such as insomnia via the Sleepio app (Luik et al., 2016) with support provided by AI and is considering increased service provision through non-statutory organisations.

Working with a group of female veterans and others with relevant expertise, this proposal has adapted Ione XSW for this specific group. Following adaptation, the aim of this proposal is to undertake a Phase II Feasibility RCT to explore potential effectiveness, engagement and wider methodological factors of IonaFFV compared to a SHAM control app (Iona SHAM CONTROL). If data suggests IonaFFV has potential to be effective and is acceptable, the study may be used to inform a subsequent Phase III Definitive RCT to treat depression in female veterans. If the app demonstrates acceptability, is engaging and shows promise to be effective, it offers a scalable way to overcome treatment barriers for all female veterans that have currently been underserved.

### 2 RESEARCH QUESTION

**Principal research question:** What are the methodological uncertainties and feasibility challenges in conducting a definitive RCT of the adapted IonaFFV app for female veterans?

**Secondary research question:** Is there potential for the adapted IonaFFV for female veterans to be effective for the treatment of depression and anxiety, is it engaging and acceptable?

### 3 STUDY OBJECTIVE

**Principal objective:** The principal research objective of the Phase II feasibility RCT is to understand methodological uncertainties (e.g., recruitment) associated with running a definitive RCT and to understand intervention acceptability and engagement.

**Secondary objective**: The secondary research objective of the Phase II feasibility RCT is to understand whether there is a potential for the adapted Iona app for female veterans to be effective for the treatment of depression and anxiety.

### 4 KEY WORDS

mCBT, low-intensity, Armed Forces, female veterans, adaptation, AI, app, feasibility, RCT

### 5 STUDY SUMMARY

| **Title** | Feasibility evaluation of a smartphone based Cognitive Behavioural Therapy (CBT) intervention for the treatment of low mood or support for worry management in female armed forces veterans in England, Wales, and Scotland. | |
| --- | --- | --- |
| **Internal ref. no. (or short title)** | Iona female veterans | |
| **Clinical Phase** | II | |
| **Trial Design** | Feasibility RCT with acceptability and usability questionnaire  Parallel group design with randomisation conducted using block randomisation (blocks of 3) and the trial is conducted with an exploratory framework. | |
| **Trial Participants** | Female forces veterans | |
| **Planned Sample Size** | 60 (30 participants per group) | |
| **Treatment duration** | 6 weeks | |
| **Follow up duration** | End of 6-week intervention engagement period and 4 week follow up (10 weeks post randomisation) | |
| **Planned Trial Period** | 10 weeks post-randomisation | |
|  | **RCTs & measures** | **Outcome domains** |
| **Primary/Feasibility/Methodological Outcomes** | Consented, recruited, completed screening, recruitment method, measure completion (baseline, 6 weeks, 10 weeks), drop out, drop out reason | Feasibility |
| **Secondary Outcomes** | PHQ-9/GAD7  Work and Social Adjustment Scale (WSAS) | Depression/Anxiety dependent on lower score on outcome measure at baseline determining severity.  Functioning |
| **Acceptability** | Mobile Acceptability and Usability Questionnaire (MAUQ) | Acceptability and Usability |
| **Intervention** | Intervention: IonaFFV for depression engaged with for 6 weeks intervention engagement period  Control: Iona SHAM CONTROL app developed to match engagement time | |
| **Route of Administration** | Iona app (IonaFFV) for the treatment of depression or Generalised Anxiety Disorder | |

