### 10.2 Outcome measures

**Table 11 Outcome measures**

| **Measure** | **Description** | **Reliability and Validity** |
| --- | --- | --- |
| **Primary/Feasibility/Methodological Outcomes** | | |
| **Feasibility** | To collect data on number of participants consented, recruited, completed screening, and to assess recruitment method, measure completion (baseline, 6 weeks, 10 weeks), drop out, drop out reason | NA |
| **Secondary Outcomes** | | |
| **Patient Health Questionnaire-9** (**PHQ-9**; Kroenke et al., 2001) | 9-item participant rated questionnaire assessing frequency of symptoms of depression over the last 2 weeks. 4-point scale for each item, with anchors at 0=not at all, 1 = several days, 2= more than half the days, 3 = nearly every day. Unidimensional scale. Available in English, Spanish, German, and Dutch versions. | Leading measure of depression widely used in clinical trials, clinical practice, and as part of the NHS Quality and Outcomes Framework (QOF) for UK primary care and Improving Access to Psychological Treatments (IAPT) Minimum Data Set (MDS). Cronbach’s α =0.89 in primary care, test-retest reliability (ICC) 0.84 after 48 hours. Validation studies indicate positive correlations with measures of functional status (r=0.73), disability days (r=0.39), and symptom-related difficulty (r=0.55) At cut-off of ≥ 10, excellent specificity (0.88) and sensitivity (0.88) with diagnoses of major depression by structured interview, replicated in a UK population (sensitivity 0.80; specificity 0.92). |
| **Generalised Anxiety Disorder-7 (GAD-7**; Spitzer et al., 2006) | 7-item participant rated questionnaire assesses frequency of symptoms of anxiety over the last 2 weeks. 4-point scale for each item, with anchors at 0=not at all, 1 = several days, 2= more than half the days, 3 =nearly every day. Unidimensional scale. Available in English, Spanish, German, and Dutch versions. | Leading measure of anxiety widely used in clinical trials, clinical practice, and as part of the UK NHS IAPT MDS. Cronbach’s α =0.92, test-retest reliability ICC = 0.83. Convergent validity good, r =.72 with Beck Anxiety Inventory, r = 0.74 with Symptom Checklist-90 anxiety scale. |

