### 10.3 Timeframe for administration of demographic and outcome measures

**Table 12 Outcome measures timeframe**

|  | **Time Period** | | |
| --- | --- | --- | --- |
| **Outcome Measure** | **Baseline (second screening)** | **6 Weeks Post Treatment Start (Treatment End)** | **10 Week Post Treatment Start (Study End Point)** |
| **Demographic** | **X** |  |  |
| **Primary Outcome (Either Dependent on Second screening/Baseline Severity - Other Secondary)** | | | |
| **PHQ-9** | **X** | **X** | **X** |
| **GAD-7** | **X** | **X** | **X** |
| **Secondary Outcomes** | | | |
| **WSAS** | **X** | **X** | **X** |
| **MAUQ** |  |  | **X** |
| **Feasibility Outcomes** |  |  | **X** |

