### 10.4 Primary endpoint/outcome

The primary endpoint of the trial is at 6 weeks post treatment start (treatment end).

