### 11.3 Statistical analysis plan

A detailed statistical analysis plan (SAP) is to be produced; the main points of the statistical analysis are summarised here. All participants will be included in each analysis, separated by arm. Missing data will be reported descriptively. No imputation will be performed due to the feasibility nature of the study, but patterns of missingness will be explored to inform future trial design.

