### 11.5 Primary analysis

Primary analyses will be conducted on methodological and feasibility data, such as recruitment rate and source, completion of baseline measures, study attrition etc. For outcomes related to study feasibility (see Table 10).

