### 11.6 Secondary analyses

Will be undertaken on either the PHQ-9 or GAD-7, the WSAS and MAUQ (see Table 12 for administration timepoints).

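### The symptom outcome is ranked and selected inconsistently (PHQ-9 or GAD-7, by lower score or by severity, primary or secondary), so the selected outcome has no defined effect estimate

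*Protocol*

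**What the plan says.** The protocol addresses the rank and the choice of the symptom outcome in several places.

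- **Section 5, Table 7.** PHQ-9/GAD-7 sit in the row for secondary outcomes, with the domain given as "Depression/Anxiety dependent on lower score on outcome measure at baseline determining severity".
- **Section 10.2, Table 11.** PHQ-9 and GAD-7 are two separate entries under secondary outcomes, with no selection rule.
- **Section 10.3, Table 12.** Both scales stand under the label "Primary Outcome (Either Dependent on Second screening/Baseline Severity - Other Secondary". Both are marked for collection at baseline, 6 weeks and 10 weeks.
- **Section 10.4.** "The primary endpoint of the trial is at 6 weeks post treatment start (treatment end"). No variable is named.
- **Section 11.5.** "Primary analyses will be conducted on methodological and feasibility data".
- **Section 11.6.** Secondary analyses: "Will be undertaken on either the PHQ-9 or GAD-7, the WSAS and MAUQ".
- **Section 11.3.** "All participants will be included in each analysis, separated by arm".

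Section 11.7 promises effect sizes and confidence intervals between the arms. Section 11.1 intends the data to inform the sample size of a definitive trial.

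**The concern.** There are two faults. The first is rank: the symptom scales cannot be primary in one table and secondary in two others and in the analysis section, with feasibility primary as well. The second is definition. One place selects on the lower baseline score, another on severity with no direction or cut-off, another says only that one or the other will be used, and another lists both. A lower score on these scales means fewer symptoms, so a lower-score rule does not fit a choice meant to reflect severity.

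The protocol does not say how scores on scales of different length are compared, what happens with ties, or how women assigned to different scales are combined. An SAP could add detail, but it could not follow all of these statements at once.

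At stake is the secondary objective in section 3 (potential effect on depression and anxiety) and the use of the results in section 11.1. A future sample size needs an SD and a plausible difference on one named scale. A selected or mixed outcome supplies neither.

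**Working it through.** The protocol gives no sample size, power or precision figure, so there is nothing to reproduce. The check compares the statements and then tests how much the selection rule matters.

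**1. Statements side by side**

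| Place | Rank of PHQ-9/GAD-7 | Choice of scale |
| --- | --- | --- |
| Section 5, Table 7 | Secondary | Lower baseline score |
| Section 10.2, Table 11 | Secondary, both listed | None |
| Section 10.3, Table 12 | One primary, the other secondary | Baseline severity, no direction |
| Section 11.5 | Not primary (feasibility is) | Not addressed |
| Section 11.6 | Secondary analysis | One or the other |

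**2. Units.** Table 11 describes the PHQ-9 as a "9-item participant rated questionnaire assessing frequency of symptoms of depression over the last 2 weeks" and the GAD-7 as a "7-item participant rated questionnaire assesses frequency of symptoms of anxiety over the last 2 weeks". Items on both are scored 0 to 3, so the ranges are 9 × 3 = 27 and 7 × 3 = 21. A mean or SD over women measured partly on one and partly on the other has no unit.

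**3. What a lower-score rule selects.** Table 8 admits PHQ-9 scores of 5-19 (15 values) and GAD-7 scores below 15, that is 0-14 (15 values), giving 15 × 15 = 225 pairs.

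- GAD-7 lower: for PHQ-9 = 5 to 14 there are 5 + 6 + … + 14 = 95 pairs, and for PHQ-9 = 15 to 19 there are 5 × 15 = 75. Total 170 (76%).
- Ties: one for each value 5 to 14, so 10 (4%), with no rule.
- PHQ-9 lower: 225 − 170 − 10 = 45 (20%).
- If severity means the higher score, the choice reverses in 170 + 45 = 215 pairs (96%).
- GAD-7 selected at 0-4: 5 values × 15 PHQ-9 values = 75 pairs (33%), where there is little room to improve.
- If scores are compared as a share of the scale maximum (27 and 21) instead of raw, the choice reverses in 22 pairs (10%).

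Each pair counts once here. This shows how the rule behaves and is not a forecast of the sample.

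**4. Sensitivity with assumed distributions.** Assumptions, none from the protocol: bivariate normal, mean PHQ-9 11, mean GAD-7 7, 9 or 11, SDs about 5, correlation 0.4 to 0.75, rounded and cut to the Table 8 limits. The lower-score rule selects GAD-7 in 53-88% of women and PHQ-9 in 7-35%, with ties in 5-12%. The mean baseline of the selected score is 6.4-8.8 under the lower-score rule and 11.3-12.0 under a higher-score rule.

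**5. Precision if each scale is analysed in everyone.** The 95% CI half-width in SD units is t(0.975, 2n − 2) × √(2/n). With n = 30 per arm and complete data this is 0.52 SD for each scale.

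**The case against.** The strongest reply is that usable estimates remain available. Both scales are collected from every participant at all three time points, Table 11 lists them separately, section 11.3 puts all participants in each analysis, and Table 12 keeps the unselected scale as secondary. All of that stands, and it limits the point in four ways.

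- A reader might infer that no coherent effect estimate can be produced, or that collected data are thrown away. The documents do not support this. Only the selected outcome lacks a definition.
- A reader might infer that the sample will be split by assigned scale, which at 15 v 15 would widen the half-width to 0.75 SD. No section describes such a split, and section 11.3 points the other way.
- A reader might expect selection on a baseline score to bias the comparison through regression to the mean. That selection precedes randomisation and acts on both arms alike. It can distort change scores and SDs, but does not by itself bias the between-arm contrast.
- A reader might see a conflict in scheduling feasibility outcomes at week 10. Table 10 (Feasibility Outcomes) includes 10-week completion, which can be counted only then.

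Selection for each participant is also the natural reading of the wording but is not stated outright. If one scale were chosen for the whole trial, the unit problem would go, but the direction and basis of the choice would still be undefined.

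Finally, symptom efficacy is a secondary, exploratory aim with no powered test. This lowers the severity without removing the contradictions.

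**Conclusion.** The point holds as an inconsistency in the rank and definition of the symptom outcome. The conflict is in the wording and rests on no assumed distribution. Its practical size is that the unstated direction of the rule decides the scale in 215 of 225 eligible score pairs, and the one direction that is written points to GAD-7 in 170 of them. These counts assume that raw scores are compared for each woman, and they are unweighted. The selected outcome therefore has no defined effect estimate or SD to carry into a definitive trial, while separate estimates for each scale can be had from the data already planned. The feasibility results do not depend on this rule. Severity: should-fix.

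**What to change.** 1. State once, and repeat consistently in sections 5, 10.2-10.5, 11.5 and 11.6 and in Table 12, that the feasibility outcomes are primary.
2. Name PHQ-9, GAD-7 and WSAS as separate secondary outcomes, each analysed in all randomised participants at week 6 (main) and week 10, preferably adjusted for that scale's own baseline value. The adjustment can be left to the SAP.
3. Delete the lower-score rule in Table 7, the one-or-the-other wording in section 11.6, and the primary label with its severity rule in Table 12.
4. Reword section 10.4 so that week 6 is the main time point for the symptom outcomes and not a primary endpoint without a variable.

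The cost is protocol wording only. No additional data collection is needed, because both scales are already scheduled for everyone at all three time points.

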**Table 7** **Study summary**

**NOTE: Secondary outcome measures and acceptability questionnaire will be collected by researchers at the University of Exeter Qualtrics platform.**

### 6 TRIAL MANAGEMENT/RESPONSIBILITIES

A dedicated Lead Researcher who holds a PhD in Social Psychology with 6 years of experience in applied mental health field from the University of Exeter (UNIEXE) and a dedicated Graduate Research Assistant (GRA) will assist with the day-to-day management of the project and be responsible for effective communication and monitoring progress. The wider Study Management Committee will have oversight of the Feasibility RCT through bi-monthly meetings via teleconference or videoconference with the PI to review progress and set targets or directly if approached by the PI or researcher to address a specific question. The trial will be registered with https://www.isrctn.com/ and assigned an ISRCTN number. Researchers have been trained in Good Clinical Practice. We will comply with the UK Policy Framework for Health and Social Care Research and UK Medical Device Regulations. The trial will be conducted to protect the human rights and dignity of participants as reflected in the 2024 version of the Declaration of Helsinki. Trial documents will be retained for a period of 10 years after the completion of the study as detailed in the Patient Information Sheet. Ethical approval will be sought by the UNIEXE Psychology Ethics committee before starting the study.

### 6.1 Participant registration/randomisation procedure

The consent and study screening process will take place on the University of Exeter password protected online Qualtrics system. Female veterans wishing to consider participation will either click on the link or scan the QR code on study advertisement to access the Participant Information Sheet. Contact information for the researcher will be provided on the Participants Information Sheet to enable potential participants to gather more information if requested. Upon receipt of a completed Consent Form, the potential participant is able to access and complete the first screening measures to determine study eligibility. Eligible participants will then be guided to complete the second screening measures to determine study suitability based on participants symptoms of anxiety and depression and well-being – PHQ9 and GAD7. Second screening will also serve as baseline measures for participants. Where inclusion criteria are met, and upon completion of the sociodemographic questions, the participant will be randomised in blocks of 3 into either of the study arms and automatically registered on to the trial. Once randomised, participants will be sent a code to download the app.

### 6.2 Data management

Only authorised UNIEXE research personnel will have access to the password protected Qualtrics database. No unauthorised access will be possible. A separate list linking codes with mobile phone number and email addresses will be kept in a secure place and only accessed by Lead Researcher. Only aggregated data will be shared with UNIEXE research team. The data will be introduced and analysed by computers. As for Internet use and monitoring by means of mobile apps, data protection systems will be designed (using secure passwords, encryption, etc.). The database is only accessible via a password. Also, to protect all information, we will follow the AES (Advanced Encryption Standard) strategies for personal password use and data encryption. The study researchers will not reveal data from which personal and health information about the participants could be deduced. The same principles will be taken into consideration in the dissemination of data in the publication of scientific papers and the presentation of research reports at scientific conferences.

